### Data collection and follow-up

Data will be collected at baseline and after fourth week. The researcher will take yoga classes at the Public Health Lab of the Department of Community and Family Medicine, and compliance will be monitored by recording the daily attendance of participants. If a subject cannot attend at least 4 days a week, he/she will not be included in the analysis.

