## Abstract

Burnout among healthcare workers is a significant global concern that affects their well-being and professional efficacy. Yoga has shown promise in reducing burnout and improving mental health outcomes. However, due to their hectic schedules, healthcare workers often struggle to find time for self-care. A 20 min yoga module has been developed specifically for them to address this. So, this study aims to assess the efficacy of a specific 20 min yoga module in reducing burnout among healthcare workers. An open-label, two-arm, randomised controlled trial involving healthcare workers aged 20–35 years participating for 4 weeks. Exclusion criteria included recent illness, respiratory ailments, pregnancy, life-threatening medical conditions or physical inability to perform yoga. After randomisation of 108 participants, they will be equally allocated to either the yoga group (20 min yoga) or the control group (20 min medium-paced walking). The primary outcome will be burnout, whereas the secondary outcomes include stress, anxiety, selective attention and happiness. Data collection: at baseline and after 4 weeks of intervention, compliance is monitored via daily attendance records. Descriptive and inferential analyses will employ intention-to-treat and per-protocol analysis using SPSS 26.0. A study with 20 participants found that a 20 min yoga intervention significantly improved emotional exhaustion, depersonalisation, personal accomplishment, happiness and Spielberger’s State-Trait Anxiety/Six-letter cancellation test scores. Cortisol levels showed trends of reduction but were not significant. These results inform the upcoming main trial. Ethical approval is obtained from the Institutional Ethical Committee via letter number AIIMS/IEC/20/762. The trial findings will be shared through peer-reviewed publications and presentations at conferences. Trial registration number: CTRI/2021/01/030568; Clinical Trial Registry of India.

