#### Control group

20 min medium-pace walking with 1600–2400 steps in 20 min, in a day for 4 weeks, will be provided as an intervention for reducing burnout among participants of this group. This walking intervention is metabolically matched to ensure comparability with other physical activity interventions, making it a suitable comparator. To check adherence and establish equality, all participants will download the free health app Google Fit.^13^ The Google Fit app will monitor the steps taken and walking duration.

A description of the interventions using the Template for Intervention Description and Replication checklist is provided in table 3.

**Table 3 T3:** Description of interventions using the TIDieR checklist

Brief name	20 min yoga module’^9^ for the yoga group and 20 min medium-pace walking for the control group
Why	The 20 min yoga module helps reduce burnout and stress among healthcare workers by promoting relaxation through simple movements, breathing and mindfulness. It provides a quick break during busy shifts, easing tension, boosting focus and improving overall well-being. Regular practice can support long-term stress relief and better mental health.
What materials and procedures	Participants in the intervention group will attend 20 min offline yoga sessions 5 days a week for 4 weeks at AIIMS Rishikesh’s public health lab. The control group will engage in medium-paced walking for 20 min 5 days a week, aiming for 1600–2400 steps per session. They will use the Google Fit app to track their steps, distance and duration and submit daily screenshots of the data.
Who provided	The researcher, a certified yoga instructor, will take the yoga sessions, while participants in the control group will practice medium-paced walking independently, with monitoring by the researcher.
How	Participants in the intervention group will attend offline yoga sessions, while those in the control group will engage in medium-paced walking at their convenience.
Where	Offline yoga sessions will occur at the Public Health Lab of the Department of Community & Family Medicine, AIIMS Rishikesh. At the same time, medium-paced walking can be done at home or the workplace, depending on the participant’s convenience.
When and how much	Yoga sessions and medium-paced walking will be performed for 20 min 5 days a week over 4 weeks.

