### Analysis of outcomes

Intention-to-treat (ITT) and per-protocol analyses will be performed to provide a comprehensive understanding of intervention effects. The proportions and means will be calculated for descriptive analysis. The normality of the data will be checked using the Shapiro-Wilk test. Continuous data will be reported as mean±SD and compared using an independent t-test. Categorical data will be reported as frequencies and compared using the χ^2^ test. An independent t-test will compare pre and postintervention data of all group outcomes. A paired t-test will be used to compare the pre and postdata of all outcomes within the group. Statisticians will be blinded to group assignments for statistical analysis. Statistical calculations will be performed by SPSS V.26.0.

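### The 4-days-a-week attendance rule drops participants from the analysis without limiting this to the per-protocol set, which contradicts the promised ITT analysis

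*Protocol article*

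**What the plan says.** The Analysis of outcomes section states: "Intention-to-treat (ITT) and per-protocol analyses will be performed to provide a comprehensive understanding of intervention effects". The Abstract repeats this: "Descriptive and inferential analyses will employ intention-to-treat and per-protocol analysis using SPSS 26.0". Neither place defines the two sets.

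The Data collection and follow-up section describes the yoga classes at the Public Health Lab, says that "compliance will be monitored by recording the daily attendance of participants", and then adds: "If a subject cannot attend at least 4 days a week, he/she will not be included in the analysis". No analysis set and no arm is named. The Abstract mentions attendance for the trial as a whole: "compliance is monitored via daily attendance records".

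Both arms are prescribed 5 days a week for 4 weeks (Table 3). Delivery differs: "participants in the control group will practice medium-paced walking independently, with monitoring by the researcher". On walkers' records, Table 3 says: "They will use the Google Fit app to track their steps, distance and duration and submit daily screenshots of the data". The Control group section also says: "To check adherence and establish equality, all participants will download the free health app Google Fit". No number of walking days is given below which a walker would be removed.

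**The concern.** An ITT analysis keeps every randomised participant in the assigned arm whatever the attendance. A rule that takes low attenders out of the analysis, without saying which analysis, cannot be carried out alongside it. As printed, an analyst could use the rule to justify an adherer-only set as the main population.

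The stake is the protection that randomisation gives. Attendance is observed after allocation and may be related to workload, and so to burnout. Yoga requires presence at one place, whereas walking can be done at home or at work. The people retained in each arm may therefore differ in ways unrelated to the intervention. Recruitment to the main trial is described as ongoing (Sampling), so the wording can still be settled before the data are analysed.

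**Working it through.** **1. The texts side by side.**
- Abstract and Analysis of outcomes: ITT and per-protocol, both to be done.
- Data collection and follow-up: below 4 days a week, out of the analysis.
- If the rule covers every analysis, the ITT set loses randomised participants for a post-randomisation reason and is no longer ITT. If the rule covers only the per-protocol set, the texts agree, but the article does not say so.

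The contradiction is textual and needs no calculation. The steps below only show what could follow from it.

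**2. The plan's own sample size.** Inputs from Sample size: effect size 0.60, alpha 0.05 (two-sided assumed, since the article does not say), power 0.80, attrition 15%, 54 per arm. The two-sample t-test needs 44.6, so 45 per arm. Then 45/0.85 = 52.9, so 53 per arm or 106 in total, against the stated 108. The figure reproduces to within 2 participants. After 15% attrition, 54 × 0.85 = 45.9, about 46 per arm, and power is 0.81. With all 54 per arm analysed it is 0.87.

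**3. Would the rule remove more than 15%?** The article gives no attendance rate. Assume that each session is attended independently with probability q, and that the rule must be met in all four weeks. The share retained is P(Binomial(5, q) ≥ 4)^4. Power is at effect size 0.60, starting from 54 per arm.

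| q | Retained | n from 54 | Power, both arms filtered | Power, yoga only filtered (54 walkers) |
|---|---|---|---|---|
| 0.95 | 0.977^4 = 91% | 49.3 | 0.84 | 0.85 |
| 0.90 | 0.919^4 = 71% | 38.4 | 0.74 | 0.80 |
| 0.85 | 0.835^4 = 49% | 26.3 | 0.57 | 0.70 |

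At 95% attendance the loss is 9%, inside the allowance. At 90% it is 29%, outside it, yet power still reaches 0.80 if only the yoga arm is filtered. The result depends entirely on the assumptions.

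**4. Possible bias.** Assume that the true difference is zero, that only the yoga arm is filtered, that its lowest attending fraction f is removed, and that attendance and improvement are bivariate normal with correlation ρ.
- Shift in SD units: ρ × φ(z_f)/(1 − f), where z_f is the f-quantile of the standard normal.
- Standard error in SD units: √(1/[54(1 − f)] + 1/54).
- Two-sided error rate, normal approximation, with r = shift/SE: P(Z > 1.96 − r) + P(Z < −1.96 − r).

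For f = 0.15: φ(−1.036)/0.85 = 0.233/0.85 = 0.274; SE = √(1/45.9 + 1/54) = 0.201.
For f = 0.30: φ(−0.524)/0.70 = 0.348/0.70 = 0.497; SE = √(1/37.8 + 1/54) = 0.212.

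| f | ρ | Shift (SD) | Error rate |
|---|---|---|---|
| 0.15 | 0.1 | 0.03 | 5.2% |
| 0.15 | 0.5 | 0.14 | 10.5% |
| 0.30 | 0.1 | 0.05 | 5.6% |
| 0.30 | 0.5 | 0.25 | 21.6% |

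Neither f nor ρ is in the article. The positive sign of ρ, which makes the shift favour yoga, is also an assumption.

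**The case against.** The best defence is that the sentence is a misplaced per-protocol definition. ITT is promised twice, a per-protocol analysis needs an adherence threshold, and this sentence supplies one directly after the compliance sentence and outside the analysis section. That is a natural reading, and it may be what was meant. It does not remove the conflict: both statements are printed, so shortening into an article does not explain it, and the reader is not told which analysis the rule governs.

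A reader might go further and infer three things that the document does not support.
- **That the main result becomes a completer comparison.** ITT is still promised and no set is named as primary. The rule also selects on attendance, so it concerns adherers rather than completers.
- **That the exclusion hits only the yoga arm.** The rule says a subject and names no arm, all participants install the app, and walkers are monitored through daily screenshots, so the rule could be applied to them. What stands is that no walking threshold is written down. The pilot does not suggest heavier loss from yoga: of 20 randomised, 9 yoga and 8 control participants completed.
- **That the result is biased towards yoga and the planned power is lost.** The outcome is change in burnout, and the most burnt-out staff may have the most room to improve, so removing them could also work against yoga. Losses stay inside 15% under the 95% attendance assumption. Adding a separate 15% dropout on top of the attendance loss would risk counting the same people twice.

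It can also be said that nothing in the article states that non-attenders go unassessed, and that naming the primary set is commonly left to the SAP. Both are fair. They bear on how much of the fix is clarification, not on whether the two texts conflict.

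**Conclusion.** The point holds as a contradiction between printed statements. Applied literally, the attendance rule leaves no true ITT population and permits an adherer-only comparison, possibly with different selection in the two arms. This is a wrongly worded rule, not a missing detail, and it needs correcting because it decides who is analysed for the primary burnout outcome.

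No size of bias follows from the document. The range of 0.03-0.25 SD, with an error rate of about 5-22%, is an illustration. It rests on exclusion from the yoga arm alone, 15-30% excluded, an attendance-outcome correlation of 0.1-0.5 and a true difference of zero. Whether losses pass the 15% allowance, or power falls below 0.80, is likewise open.

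**What to change.** - Reword the sentence in Data collection and follow-up so that the 4-days-a-week rule defines the per-protocol set only, and give walkers an equivalent criterion based on their Google Fit records.
- In Analysis of outcomes, state that the ITT analysis includes everyone randomised, in the assigned arm, whatever the attendance, and that the conclusion on burnout follows it.
- Ask participants who stop attending to complete the end-of-intervention assessments that are already planned.

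The cost is a change of wording in two paragraphs and some extra follow-up effort. The estimated effect may be smaller, because participants who did little of the intervention stay in. For example, if 15% of the yoga arm gained nothing, an effect of 0.60 would become 0.60 × 0.85 = 0.51, and power with 54 per arm would be 0.75 instead of 0.87.

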## Results of the pilot study

A pilot study was conducted to evaluate the feasibility of an intervention. The quality of practice was assessed using a 10-point Likert visual analogue scale, with participants achieving an average mean score of 9 out of 10. This high score indicates strong acceptability among participants, demonstrating their comfort and ability to perform the practices included in the yoga module effectively.

A total of 20 participants were recruited for the pilot study, and informed consent was obtained from each participant. The participants, with a mean age of 31.6±5.3 years, were randomly assigned to either the yoga group (20 min yoga session) or the control group (20 min medium-paced walking). The interventions were delivered in offline classes and conducted at least 5 days a week over 4 consecutive weeks. Burnout scores were measured using the MBI, salivary cortisol levels were assessed with the ELISA technique and happiness scores were assessed using a self-rated happiness scale at baseline and after the 4-week intervention. State anxiety and selective attention were assessed using the STAI and SLCT, respectively, before and after the 20 min intervention at both baseline and after the 4 week intervention. Normality was checked with the Shapiro-Wilk test. Paired and independent t-tests were used for normally distributed data, while the Wilcoxon Signed Rank and Mann-Whitney U tests were used for non-normally distributed data.

Seventeen participants (nine from the yoga group and eight from the control group) completed the intervention. Statistical tests revealed a statistically significant improvement in scores in all the domains of burnout in the yoga group compared with baseline, as shown in table 4. Significant changes were found in EE (p=0.009), DP (p=0.028), and PA (p=0.03) in the yoga group. In contrast, no significant changes were observed in the control group across these domains: EE (p=0.31), DP (p=0.28), and PA (p=0.68).

**Table 4 T4:** Pre and postmean scores of MBI, salivary cortisol, happiness scale, STAI and SLCT in healthcare workers after 4 weeks of intervention

			Yoga group	Control group	P value
MBI					
Emotional exhaustion	Day 0	Pre	24.67±7.05	22.75±8.81	0.631*
	Day 29	Post	19.44±7.09	21±9.18	0.705*
		P value	0.009†	0.31†	
Depersonalisation	Day 0	Pre	7±5.72	5.5±2.98	0.481‡
	Day 29	Post	4.33±3.77	4±3.42	0.423‡
		P value	0.028§	0.324§	
Personal accomplishment	Day 0	Pre	26.56±8.08	24.5±12.92	0.705*
	Day 29	Post	29.56±8.68	26±12.2	0.506*
		P value	0.037†	0.683†	
Salivary cortisol					
Concentration (ng/mL)	Day 0	Pre	77.89±17.5	71±20.97	0.477*
	Day 29	Post	63.11±25.07	64.13±26.58	0.937*
		P value	0.078†	0.486†	
Happiness scale					
Scores	Day 0	Pre	7.5±1.04	7.8±0.8	0.579*
	Day 29	Post	8.5±1.04	8±1.2	0.218*
		P value	0.007†	0.197†	
STAI					
Scores	Day 1	Pre	35.89±4.05	34.59±3.14	0.469*
		Post	32.66±3.16	34.76±3.33	0.205*
		P value	0.071†	0.922†	
	Day 28	Pre	38.79±5.23	32.04±7.25	0.049*
		Post	30.9±3.28	29.51±5.92	0.566*
		P value	0.017†	0.154†	
SLCT					
Scores	Day 1	Pre	25.89±6.58	26.54±4.89	0.82*
		Post	31.78±7.55	25.06±2.62	0.031*
		P value	0.021†	0.418†	
	Day 28	Pre	32.78±7.6	28.88±8.51	0.338*
		Post	38.67±9.49	30.38±6.95	0.057*
		P value	0.001†	0.255†	

P < 0.05 considered statistically significant.

* Independent t test.

† Paired t test.

‡ Mann-Whitney U test.

§ Wilcoxon Signed Rank Test.

MBI, Maslach Burnout Inventory; SLCT, Six Letter Cancellation Test; STAI, State Trait Anxiety Inventory.

The yoga group showed a trend towards reduced salivary cortisol levels (14.78±21.96 ng/mL), but this change did not reach statistical significance (p=0.078). The control group experienced a smaller decrease in salivary cortisol levels (6.87±26.43 ng/mL), which also did not reach statistical significance (p=0.48), as shown in table 4. Additionally, the yoga group had a significant (p=0.007) increase in happiness scores. Mean pre–post scores of the happiness scale are shown in table 4.

Significant changes were observed in the yoga group across both STAI and SLCT scores following the intervention. On day 1, while the Yoga group showed a non-significant (p=0.071) decrease in STAI scores, there was a significant (p=0.021) improvement in SLCT scores. On day 28, while the Yoga group showed a significant reduction in STAI scores (p=0.017), there was a substantial improvement in SLCT scores (p=0.001). In contrast, the control group showed no significant changes in either STAI or SLCT scores at any time. The mean scores of STAI and SLCT on day 1 and day 28, immediately before and after the intervention, are shown in table 4.

In conclusion, the 20 min yoga intervention significantly improved burnout scores, particularly in EE, DP and PA. While trends towards reduced salivary cortisol levels were noted in the yoga group, these findings did not reach statistical significance. These results will inform the main trial that follows.

## Discussion

This is the first trial to assess the efficacy of a 20 min yoga module in reducing burnout among healthcare workers. The findings of this study contribute to the growing body of evidence supporting the effectiveness of yoga as a preventive and therapeutic intervention for burnout in healthcare settings.

The intervention incorporates components such as loosening exercises (*sukshma vyayama*), regulated breathing techniques (*pranayama*) and meditation (*dhyana*). These practices are designed to address various dimensions of burnout while also exploring secondary outcomes like stress reduction, anxiety management, selective attention and happiness. Previous research supports the effectiveness of yoga-based interventions in improving professional quality of life and reducing burnout. For instance, a randomised controlled trial conducted at a tertiary care hospital demonstrated significant improvements in EE, DP and PA among healthcare providers following a 12-week yoga-based programme (p<0.001)2.^24^ Similarly, workplace yoga programmes have reduced fatigue and burnout among blue-collar workers, highlighting their feasibility and utility across diverse occupational settings.^25^

A systematic review further corroborates the positive impact of yoga on stress management among healthcare workers, with studies reporting improvements in self-regulation, self-compassion and stress levels following yoga interventions.^26^ Additionally, the development of shorter modules, like the 20 min intervention used in this study, addresses practical barriers such as time constraints faced by healthcare workers.^9^ These findings collectively underscore the potential of yoga to enhance resilience, emotional control and cognitive functioning while fostering a sense of PA and fulfilment.

By examining primary (burnout reduction) and secondary outcomes (eg, mindfulness and happiness), this study contributes to the growing body of evidence advocating for integrating accessible yoga practices into healthcare settings. Future research could explore long-term effects and broader applications across different populations to validate these promising results.
